## Abstract

**Background:**

The automatic tendency to attend to and focus on substance-related cues in the environment (attentional bias), has been found to contribute to the persistence of addiction. Attentional bias modification (ABM) interventions might, therefore, contribute to treatment outcome and the reduction of relapse rates. Based on some promising research findings, we designed a study to test the clinical relevance of ABM as an add-on component of regular intervention for alcohol and cannabis patients.

**Design/Methods:**

The current protocol describes a study which will investigate the effectiveness and cost-effectiveness of a newly developed home-delivered, multi-session, internet-based ABM (iABM) intervention as an add-on to treatment as usual (TAU). TAU consists of cognitive behavioural therapy-based treatment according to the Dutch guidelines for the treatment of addiction. Participants (*N* = 213) will be outpatients from specialized addiction care institutions diagnosed with alcohol or cannabis dependency who will be randomly assigned to one of three conditions: TAU + iABM; TAU + placebo condition; TAU-only. Primary outcome measures are substance use, craving, and rates of relapse. Changes in attentional bias will be measured to investigate whether changes in primary outcome measures can be attributed to the modification of attentional bias. Indices of cost-effectiveness and secondary physical and psychological complaints (depression, anxiety, and stress) are assessed as secondary outcome measures.

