#### Other measurements

During the baseline assessment, sociodemographic information will be collected, such as gender, relationship, level of education, and work. Furthermore, details of the patients’ own clinical history of addiction as well as of their family will be asked. Next, participants who are assigned to one of the training conditions will be asked about their expectations of the intervention. Before and after each training session, participants will rate their intensity of craving on a visual analogue scale (VAS), varying from 0 (no craving at all) to 100 (extreme craving). With this, possible direct effects of the intervention on subjective craving can be examined. Furthermore, at the end of the baseline assessment, all participants are asked to fill in a short questionnaire about their computer/laptop use in their private life. This information might be helpful when investigating for whom this iABM intervention was effective. Last, after the first week of training and during the post-assessment, participants, who are assigned to one of the training conditions, will be asked to fill in an evaluation questionnaire, in which they can give their opinion about the intervention and are asked to indicate whether the intervention helped them. Information derived from these questionnaires can be used as indications for possible next steps towards implementation. For an overview of all questionnaires and tasks per time point, see Table 2.

**Table 2 Tab2:** Overview of measurement instruments per time point

Purpose	Measures	Baseline	Post-assessment	Follow-up
Attentional bias assessment	Odd one out task	X	X	X
Baseline measures	Demographics	X		
	History of addiction	X		
	Family history of addiction	X		
Primary outcome measures - clinical	MATE (substance use, craving)	X	X	X
	Clinical state (relapse)			X
Primary outcome measures - Societal/economical	TiC-P	X	X	X
	EQ-5D	X	X	X
Secondary outcome measures	MATE (depression, anxiety and stress)	X	X	X
	Computer use	X		
Others	Expectation-questionnaire	X^a^		
	Training evaluation		X^a^	

^a^only to be filled in by participants in one of the training conditions

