### Primary and secondary outcome measures

The effectiveness of the iABM intervention will be examined by changes in substance use (i.e. quantity of use in the past 30 days), craving, and relapse rates. Measurements of attentional bias will serve as a manipulation check for the effects of iABM intervention.^1^ Secondary outcome measures are cost-effectiveness,^2^ and secondary physical and psychological complaints (depression, anxiety, and stress). The evaluation forms of the patients and therapists will be assessed as well.

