### Sample size

To find a difference between groups of medium effect size with a power of 0.8 at an alpha of 0.05, both the treatment and the control arm need to include 64 patients, as calculated with.

G*power 3.1.5. Dropout rates in regular addiction treatment are known to be approximately 20%. Given the 6 and 12 months follow-up measurements a dropout rate of 40% was calculated. Therefore, a total amount of 213 patients will be recruited.

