### Randomization

Participants who meet the inclusion criteria will be automatically assigned to one of the three conditions with the following likelihood (1) 50% TAU + iABM, (2) 25% TAU + placebo condition and (3) 25% TAU-only. Furthermore, the registration and monitoring system stratifies for gender, age group (18–30, 30–50, 50+), type of addiction, and institution. Therefore, participants are assigned to one of the three conditions to which the fewest participants of their gender, age group, and type of addiction are assigned accounting for the institution of the participants. When proven effective, participants in the control conditions (TAU + placebo condition and TAU-only) will be offered the iABM intervention after the end of the study (approx. End 2018).

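### Three primary outcomes have no order or success rule, so the alpha of 0.05 and power of 0.80 are not tied to the undefined verdict of effectiveness that triggers later steps

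*Protocol article*

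**What the plan says.** **Primary outcomes.** The abstract (Design/Methods) says: "Primary outcome measures are substance use, craving, and rates of relapse". The section Primary and secondary outcome measures judges effectiveness on the same three.

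**Analyses.** Under Data analyses, Clinical analysis, substance use and craving are analysed by a 4 × 2 repeated measures ANOVA and relapse by Cox regression. No significance level, testing order or success rule is given there.

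**Sample size.** Alpha appears only in the Sample size section, which aims "To find a difference between groups of medium effect size with a power of 0.8 at an alpha of 0.05" and concludes that "both the treatment and the control arm need to include 64 patients". No outcome is named. A 40% dropout allowance brings the total to 213.

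**What depends on the result.** The Randomization section says: "When proven effective, participants in the control conditions" will be offered iABM after the study. The Economic evaluation section makes the economic evaluation conditional on iABM having been shown to work. Neither place defines that verdict.

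**Status of the economic measures.** Table 2 (under Other measurements) lists TiC-P and EQ-5D as "Primary outcome measures - Societal/economical". The section Primary and secondary outcome measures says: "Secondary outcome measures are cost-effectiveness", together with physical and psychological complaints. The abstract agrees with that section, not with the table.

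**The concern.** A trial sized for one test, with three primary outcomes and one yes/no verdict at the end, needs a rule that turns three results into that verdict. The document gives none, and its sections point to different bases for it:

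- The hypothesis (Trial objective and hypothesis) joins all three outcomes with *and*.
- The abstract's Discussion frames the question around relapse.
- Clinical analysis introduces the main hypothesis with the ANOVA on substance use and craving, and treats relapse separately.
- Economic evaluation uses substance use and relapse, without craving.

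If the results are mixed, the outcome that supports a claim of effectiveness could be chosen after the data are seen. The stated alpha and power could not then both be read as properties of the trial's conclusion. The conflict over the economic measures adds doubt about which outcomes count as primary.

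**Working it through.** **Inputs from the protocol.** Alpha 0.05; power 0.80; 64 per arm; 40% dropout; total 213; three primary clinical outcomes; allocation 50:25:25, which is 1:1 for iABM against the pooled controls.

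**Assumptions.** Medium effect means d = 0.5. Testing is two-sided; this is not stated, but it reproduces 64 per arm, whereas a one-sided test would need 51. The correlation between test statistics is varied from 0 to 0.9, because the protocol gives none.

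**1. The plan's own figure.** A two-sample t-test with d = 0.5, two-sided alpha 0.05 and power 0.80 needs 63.77, so 64 per arm (power 0.801). For dropout, 2 × 64 / (1 − 0.40) = 128 / 0.6 = 213.3. Both figures reproduce as one test of one outcome, with no allowance for three.

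**2. If any one outcome suffices, each at 0.05.** For independent outcomes the false-positive rate is 1 − (1 − 0.05)³ = 1 − 0.857 = 0.143. For correlated outcomes, simulating three equally correlated normal test statistics with two-sided 0.05 limits gives:

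| Correlation | Chance of at least one false positive |
|---|---|
| 0 | 0.143 |
| 0.3 | 0.136 |
| 0.5 | 0.125 |
| 0.7 | about 0.11 |
| 0.9 | about 0.083 |

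**3. If all three must succeed, each at 0.05.** The false-positive rate is at most 0.05 without adjustment. Joint power is below 0.80. With 0.80 on each outcome it is 0.80³ = 0.51 under independence, and simulation gives a little above 0.7 at correlation 0.9.

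**4. If Holm or Bonferroni is used.** The strictest level is 0.05 / 3 = 0.0167. With 64 per arm and d = 0.5, the t-test power for a given outcome at that level is 0.66. Restoring 0.80 at that level would need 86 per arm, so 172 / 0.6 = 286.7, or 287 in total.

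The 0.66 is power for one named outcome. Holm's first step rejects if any of the three p-values is at or below 0.0167. If all three effects were d = 0.5, that would happen with probability about 0.96 (independent) to 0.75 (correlation 0.9).

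**Limit of these power figures.** They are for a t-test. They match the Sample size section but do not carry over directly to the Cox analysis of relapse.

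**The case against.** **Nothing says that each outcome is tested at 0.05 or that one success is enough.** Clinical analysis states no level, and the hypothesis is conjunctive. This stands. A reader might infer that the trial's error rate is 14%; the document does not support that as a fact. The figure applies only if any one outcome suffices, each is tested at 0.05 and the outcomes are independent. In the same patients they are probably positively correlated, which lowers it.

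**Multiplicity rules are commonly left to an analysis plan, and only a condensed article is shown.** This also stands as far as missing detail goes. What remains is in the article itself: three primary outcomes, a one-test sample size with no outcome named, and consequences tied to an undefined verdict whose basis shifts between sections.

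**The economic label is editorial.** A reader might count TiC-P and EQ-5D as two more primary tests and infer a higher error rate. That does not follow. The economic outcomes are handled by bootstrap and acceptability curves, with no significance test described. The economic evaluation also follows the verdict of effectiveness and cannot produce it. The table heading may mean the main instruments of the economic strand, and a footnote on cost-effectiveness is not legible in the copy reviewed. The label still conflicts with the text and needs reconciling, but it adds no type I error.

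**Conclusion.** The point holds as one about an unfixed decision rule. The protocol does not say how three primary outcomes lead to a verdict of effectiveness, so the stated 0.05 and 0.80 cannot both be attached to that verdict:

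- **Any one outcome suffices:** false-positive rate about 8% to 14%, not 5%.
- **All three required:** false-positive rate at most 5%, power about 0.5 to just over 0.7, not 0.80.

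These sizes assume d = 0.5 on each outcome, two-sided tests at 0.05, 64 evaluable patients per arm and correlations from 0 to 0.9. The sample size arithmetic is correct for one outcome. Separately, Table 2 contradicts the abstract and the outcomes section on whether the economic measures are primary. The change should be made, but it does not call the design into question.

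**What to change.** Before unblinding:

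1. State one rule for the three outcomes. Either the sponsor names a single primary outcome at 0.05, with the other two tested after it in a fixed order, or Holm is applied across the three.
2. Define the verdict of effectiveness in the Randomization and Economic evaluation sections by that rule.
3. In the Sample size section, name the outcome to which the power applies. With a single primary outcome, 0.80 and 213 stand. With Holm, add that per-outcome power at the 0.0167 level is 0.66 for a t-test with 64 per arm and d = 0.5. Do not present 0.66 as the power of Holm's first step.
4. Reconcile the Table 2 label for TiC-P and EQ-5D with the abstract and the outcomes section, which make cost-effectiveness secondary.

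The cost is wording. The downside is a stricter claim for the outcomes tested later in a fixed order, or a lower stated per-outcome power under Holm. No further recruitment is needed unless the sponsor wants 0.80 at the 0.0167 level.

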**Discussion:**

This randomized control trial will be the first to investigate whether a home-delivered, multi-session iABM intervention is (cost-) effective in reducing relapse rates in alcohol and cannabis dependency as an add-on to TAU, compared with an active and a waiting list control group. If proven effective, this ABM intervention could be easily implemented as a home-delivered component of current TAU.

**Trial registration:**

Netherlands Trial Register, NTR5497, registered on 18th September 2015.

## Background

Alcohol and drug use disorders are well known for their persistent character. People diagnosed with substance use disorders are usually well aware of the undesirable consequences of their substance use and, therefore, often desire to quit. However, in spite of their motivation to stop, they frequently report an inability to voluntarily control their alcohol or drug use. This loss of control is associated with high rates of relapse, which have been found to be 40–50% one year after successful treatment, rising to 70% three years later [1, 2]. These numbers indicate that current interventions might not successfully address all relevant aspects of addiction. Therefore, (cost-) effective methods of improving existing interventions need to be developed, in order to lower rates of relapse and thereby increase patients’ quality of life.

Most current interventions in addiction care, such as cognitive behavioural therapy (CBT), focus on conscious decision-making and behavioural control, such as learning how to recognize ‘risky’ situations, and to unravel and change possible ‘wrong beliefs’ about the alcohol or drug use. This restricted focus of current interventions on conscious processes might be a possible reason for their limited success rates. Accordingly, current dual process models of addiction emphasize that next to the conscious cognitive processes also more automatic processes, such as attentional bias, play a crucial role in the development and persistence of addiction [3, 4]. *Attentional bias* in substance dependency can be defined as an automatic tendency to focus attention on substance-related cues in the environment [5, 6], such as alcohol advertisement or a used joint on the street. Attentional bias for substance-related cues has repeatedly been found in different substance use disorders, such as alcohol, tobacco, and opioids dependency [7–9]; for a critical review on the role of attentional bias in addiction see [10].

Heightened attention to substance-related cues can involve two processes. The first process is attentional engagement bias, reflecting increased direction of attention towards substance-related cues. The second process is attentional disengagement bias, reflecting increased subsequent difficulty disengaging attention from substance-related cues. In addiction, both types of attentional bias appear to operate. Patients diagnosed with substance use disorder are likely to become quickly aware of substance-related cues in their environment [11], plausibly indicating that attention is spontaneously drawn towards these cues. Furthermore, heavy users seem to focus their attention longer on substance-related information than do social users [12], which suggests that heavy users experience difficulty disengaging their attention away from substance-related cues.

Both biases in attention will increase awareness of substance-related cues, which might be especially problematic for people who would like to stop or to reduce their intake of alcohol or drugs [13]. That is, patients diagnosed with substance use disorders seem to be surrounded by relatively many temptations, which makes resisting even more challenging. Recent research supports the idea that attentional bias towards alcohol and drug cues is related to the intensity and persistence of addictive behaviours. First, attentional bias has been found to increase in strength during the course of more frequent and increased use of the addictive substance [14]. In other words, the strength of attentional bias favouring substance-related cues is related to the severity of addiction. This may reflect a self-reinforcing bias-use-bias cycle, in which increased substance use induces increased attentional bias which in turn increases substance use and so on. This may render it increasingly difficult to quit the use of addictive substances. Second, higher levels of subjective craving have been found to be related to stronger attentional bias favouring substance-related cues [15]. Such increased attention to substance-related information may increase the desire to use and, as a result, interfere with the deliberate intention limiting or stopping the intake of alcohol or drugs. Third, greater attentional bias to substance-related cues prior to treatment has been shown to be related to poorer treatment outcome [16], indicating that people who display greater attentional bias to substance-related cues benefit less from current interventions than people who exhibit little or no such attentional bias. Finally, some studies have found that strong attentional bias to substance-related cues increases the risk of relapse after successful treatment [17]. Importantly, recent studies have found that this attentional bias is largely unaffected by current CBT-based interventions [11, 18], suggesting that an intervention aimed at directly reducing attentional bias to substance-related cues might add to the effects of traditional CBT.

In line with this, a new type of interventions has been developed with the specific aim of modifying biased information processes, collectively called cognitive bias modification (CBM) interventions. The subset of CBM interventions specifically targeting attentional bias are referred to as attentional bias modification (ABM) interventions. Both in the context of experimental research and clinical trials, it has been shown that attentional bias can be effectively altered using computerized procedures [17, 19, 20]. However, in order to achieve clinically meaningful effects it is important that reduced attentional bias results in changes of substance use-related symptoms. Of course, if an ABM intervention does not modify attentional bias, then no changes in symptoms or behaviour can be expected [21, 22], and ABM interventions are unlikely to be effective when attentional bias is not present prior to the intervention [23–25]. However, if an ABM intervention does result in the reduction of pre-existing attentional bias, then it becomes plausible that there also will be corresponding reduction in symptoms that are in part caused or maintained by this attentional bias, and such changes in clinical symptoms can be evaluated. It has been observed that in recent research the successful modification of attentional bias to substance-related cues has often not been transferred into these desired behavioural changes, such as reduced alcohol or drug intake or increased time until relapse [20, 26]. Therefore, it seems important to consider the factors that may moderate whether the modification of such attentional bias delivers these clinically meaningful benefits.

One important factor may be motivation to change. In most of the experimental studies in which attentional bias to substance-related cues has been modified successfully, without corresponding change in problematic substance use behaviour, participants have been non-clinical volunteers without apparent motivation to change their substance use [19, 20, 27]. To test the capacity of ABM interventions to attenuate addiction-related symptoms in clinical cohorts, it is necessary to deliver ABM interventions to samples of treatment-seeking participants; patients who are motivated to change their problem behaviour. In line with this, recent research in an outpatients clinical sample found that adding an ABM intervention to regular treatment not only led to greater reduction in attentional bias to substance-related cues, but also to longer times until relapse, when compared with a placebo control condition [17]. Such findings are consistent with the idea that, when patients are motivated to change, the direct modification of attentional bias to substance-related cues can add to the efficacy of conventional interventions.

Another factor that may moderate the efficacy of ABM interventions is the context in which the intervention is delivered. Within the field of social anxiety research, interventions designed to reduce attentional bias to social threat cues have been shown to yield beneficial effects on social anxiety when delivered in the laboratory or clinic [28, 29], but often do not deliver such benefits when administered as home-delivered interventions [30]. Typically, in the home environment, these interventions fail to alter attention to social threat cues. A possible explanation might be that people diagnosed with social anxiety disorder experience their home environment as a safe place, and do not display attentional vigilance for threat cues or experience anxiety in their home setting. This lack of anxiety and the absence of attentional bias prior to the intervention might interfere with its efficacy [31]. In line, the theory of emotional processing suggests that fear-relevant information needs to be activated in order to change it successfully [32]. In contrast, in substance use disorders the experience of craving can be expected to be experienced most strongly in the home environment, as craving is likely to be strongest within the environment in which people typically tend to use [33]. As the laboratory or clinic are novel environments, these are not likely to induce craving and thus ABM interventions might be less effective when delivered in these types of substance-use irrelevant environments. Thus, ABM interventions for substance dependency might be even more effective when delivered at home and when the experience of craving is high. However, in apparent conflict with this, a study in which an ABM intervention was delivered via the internet failed to find convincing support for its efficacy [34]. Although participants in the ABM group showed a reduction in the consumed glasses of alcohol a day, this effect could not be attributed to the intervention, because the same effect was found in the placebo control group. Importantly, this study delivered a web-based ABM intervention in the absence of any other (motivational) intervention, and participants did not intent to stop or to reduce their alcohol use. In order to clarify the effectiveness of home-delivered ABM interventions in substance dependency more research accounting for all important factors is needed.

A potentially important limitation of previous studies, which may have constrained their therapeutic impact, concerns the simplicity of current attentional training tasks that have been employed with the aim of altering real world attentional bias. Typically, these tasks have presented only two static stimuli, one of which is related to the target category of information, such as alcohol, and participants have been required to discriminate the identity of a small “probe” that appears either in the locus of this stimulus or in the locus of the other neutral stimulus. By presenting these probes distally from the target stimulus, it is hoped that participants will come to attend away from this category of information [35]. This simple task, displaying only two static stimuli, does not challenge the attentional system, and clearly lacks the dynamic complexity of real world settings, which may limit transfer of the resulting training effects to real-life situations [36]. Hence, it would be desirable to develop more complex and dynamic ABM interventions in order to train change in attentional vigilance to substance-related information that is most likely to transfer into real-world settings, and so drive therapeutic changes in substance use-related behaviour and symptoms.

Another important potential consideration is the number of training sessions that should be included in an ABM intervention. Laboratory studies have shown that a single session of ABM intervention can modify attentional bias transiently, but studies using this approach to alter attention to substance-related cues have not found generalization of such effects to new stimuli that were not employed in the training procedure nor changes in substance use-related symptoms [19, 20, 37]. This suggests that multiple sessions of ABM intervention are likely to be necessary for the modification of attentional bias to generalize to novel stimuli, and translate into relevant changes in substance use-related symptoms. In line with this, preliminary evidence shows that the modification of attentional bias to substance-related cues through multiple sessions can result in changes of substance use-related behaviour [17]. Given the need to deliver multiple training sessions to produce clinically meaningful change in symptoms, it is necessary to ensure that participant motivation is sustained. This, it may be advisable to add motivational components to the ABM intervention, either face to face or online. Such components, which may include motivational interviewing, could be designed to increase motivation to change substance use [38] or motivation to finish the ABM intervention in particular [39]. Another way to increase motivation to remain engaged in a multi-session ABM intervention would be to make the training itself more appealing, for example via gamification of the intervention [40, 41]. Of course, while such gamification is likely to increase motivation to perform the training, it may not enhance motivation to change addictive behaviour [40]. Therefore, it will be important to sustain regular treatment, including motivational components.

Based on these considerations, the current study will investigate the effects of a gamified, home-delivered, and internet-based multi-session ABM intervention as an add-on to regular face-to-face protocolled TAU. This combined treatment may strengthen the motivation to change by sustaining treatment as usual (TAU) on the one hand, while also directly reducing attentional bias favouring substance-related cues (ABM intervention) on the other hand, leading to improved treatment outcome and decreased rates of relapse.

